### Randomization and interventions

Randomization will be performed by a researcher not involved in the recruitment, assessment, or treatment of the participants by means of a random numerical sequence generated by Microsoft Excel 2010, before the beginning of the study. Treatment allocation will be concealed through sealed, opaque envelopes sequentially numbered. After the baseline assessment, one of the therapists responsible for the intervention will open the sealed envelope to identify the group to which the participant was allocated (Pilates Group or Aerobic Group). This is a single-blind study because only the assessor will be blind to the allocation of the participants in the treatment groups. Due to the nature of the interventions, it will not be possible to blind participants and therapists. At the end of the study, the assessor will say to which group he believes the participants were allocated in order to test the blinding of the study.

Both groups will receive 16 individual, twice-weekly exercise sessions lasting 60 min each over a period of 8 weeks. To improve adherence, participants will receive a calendar with the sessions date and the available days for missed sessions. This will ensure that the intervention period and the make-up sessions do not exceed 10 weeks, when the treatment will end, independently of the number of sessions achieved. Additionally, in São Paulo, older adults aged above 60 years do not pay for public transportation, which could ensure participants to come to the intervention site. Sessions will be supervised by two physical therapists. The Pilates Group will be supervised by a physical therapist certified in Pilates with four years of experience with the method, and the Aerobic Group will be supervised by a physical therapist specialized in Sports Physical Therapy with one year and six months of experience and specifically trained with the proposed exercises. Patient chart will be audited monthly for protocol deviations by an independent researcher. The treatments are described in Table 1. Patients will be asked to not look for other treatments outside the trial during the intervention period. Adverse events will be collected during the intervention period. Table 2 shows the timeline of the study.

**Table 1 Tab1:** Description of the interventions

Group	Description
Pilates	The Pilates Group will undergo a specific exercise program including modified [38] mat-based and equipment-based Pilates exercises. In the first session, participants will receive basic training on the Pilates method and power house activation, which is the isometric contraction of the transverse abdominis, multifidus, and pelvic floor muscles during expiration [12, 44]. Power house activation will always be combined with the exercises in order to stabilize low back. The session will be divided into: warm-up and global stretching (5 min), exercises for the upper and lower limbs, abdomen, and spine (45 min), global stretching (5 min), and relaxing local massage (5 min). There will be a minimum of five exercises and a maximum of 15 exercises in each session. Each exercise will be selected individually, according to the objective of the treatment and preference of the patient and adapted if patient’s pain worsens. For example, if the objective of the treatment is to strengthen gluteus muscles and patient cannot get into a desired position or feels pain, the exercise will be adapted to another position or equipment without changing its objective. The exercises will be modified so that they can be performed at three levels of difficulty: basic, intermediate, and advanced (Additional file 1: Appendix 1 and Additional file 2: Appendix 2). In the first session, the patients will perform the basic exercises. The progress to a new level of difficulty will occur whenever postural compensations decrease, and the patient can perform eight to 10 repetitions easily and without pain.
Aerobic	The Aerobic Group will be submitted to a global stretching program (lower limbs, upper limbs, and spine with two repetitions and maintenance of each stretch for 30 s in each segment [45]) for a total of 10 min, walking on the treadmill for 20 to 40 min (intensity will be increased according to individual ability and report of pain), and relaxation with local massage for 5 minutes [7]. Training intensity will be based on the combination of heart rate (based on the maximum heart rate percentage: 208 - (0.7 x age)) [46] and the rate of perceived exertion assessed through the Borg scale [47]. A percentage of 50 to 75% of the maximum heart rate and levels between 12 and 13 (moderate intensity) of the Borg scale will be used [48].

**Table 2 Tab2:** Timeline for the schedule of enrolment, interventions, and assessments

Outcomes	Enrolment	Before randomization	Intervention period (8 weeks)	8-week follow-up after randomization	6-months follow-up after randomization
Eligibility criteria	X				
Demographic data	X				
Informed consent	X				
Primary outcomes					
Pain intensity		X		X	
General disability		X		X	
Secondary outcomes					
Pain intensity			X		X
General disability					X
Global impression of improvement		X		X	X
Specific disability		X		X	X
Dynamic balance		X		X	X
Muscular strength		X		X	X
Interventions					
Pilates method treatment			X		
Aerobic treatment			X		

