### Assessment

Before assessment, written consent will be obtained from the patients. A blinded assessor, who is a physical therapist with five years of clinical experience, will evaluate the eligible participants in person. The evaluation will consist of: personal data, clinical data, and evaluation of outcomes. The initial assessment will be conducted prior to the random distribution of the patients into the treatment groups, in a reserved place. The assessment of the outcomes will be repeated eight weeks and six months after randomization in the same place. To prevent loss of follow-up, patients will be asked to be available nearly the dates of follow-ups.

The primary outcomes will be pain intensity and disability, assessed eight weeks after randomization. Secondary outcomes will be as follows: global perceived improvement, specific disability, dynamic balance, muscle strength (gluteus maximus, gluteus medius, and hip lateral rotators), and pressure pain threshold, assessed eight weeks and six months after randomization. Pain intensity and disability assessed six months after randomization will be considered as secondary outcomes too. All the questionnaires/scales used in this study show adequate measurement properties [22, 26, 27].

The pain intensity perceived by the patient in the last seven days will be evaluated by the 11-point Pain Numerical Rating Scale [22], with zero being “no pain” and 10 being “pain as bad as could be”. This scale will also be applied daily before each treatment session in relation to pain intensity in the last 24 h. The pain assessment will be conducted verbally.

Disability associated with low back pain in the last 24 h will be assessed using the Roland Morris Disability Questionnaire [22, 26, 27], consisting of 24 items that describe daily activities that patients often report difficulty performing due to low back pain. The answers are yes/no, and each affirmative answer is worth one point. The final score is calculated by adding all the points. The higher the score is, the greater the limitation.

The global perceived improvement comparing the onset of symptoms to the last few days will be assessed using the Global Perceived Effect Scale [22]. It is an 11-point numerical scale (− 5 to 5), with − 5 being “vastly worse”, 0 “no change”, and 5 “completely recovered”.

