Isometric muscle strength will be assessed using a dynamometer (Lafayette Instrument Company, Indiana, United States). The gluteus medius, gluteus maximus, and lateral hip rotators will be assessed bilaterally, since these muscles are directly related to pelvic stabilization [33]. The gluteus medius muscle will be evaluated with the participant in lateral decubitus with the test leg upwards, and hip in neutral adduction and extension [34]. Resistance to movement will be applied using a non-elastic strap and the handheld dynamometer, which will be 5 cm above the lateral epicondyle of the femur. The gluteus maximus muscle will be evaluated with the patient in the ventral decubitus position with hip neutral and knee flexed at 90 degrees [35]. Resistance to movement will be applied using a non-elastic strap and the handheld dynamometer, which will be 5 cm above popliteal region. The hip lateral rotator muscles will be assessed with the participant sitting on the stretcher with hips and knees flexed at 90 degrees, upper limbs crossed over the trunk, and hip positioned in slight lateral rotation with the medial malleolus aligned with the midline of the body [35]. Resistance to movement, using a non-elastic strap and the handheld dynamometer, will be applied 5 cm above the medial malleolus. Two submaximal force tests will be performed to familiarize the participant with each test position, followed by two repetitions with maximum isometric contraction for each muscle group and the analysis will use the average of the two maximum contractions [36]. The intrarater reliability of isometric muscle strength was tested prior to data collection and was adequate (ICC above 0.81 for the three muscular tests).

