Pressure pain threshold evaluates the lowest stimulus in which a patient perceives pain [37] and will be measured using a digital pressure algometer (Somedic Inc., Hörby, Sweden®). For the algometry, marks will be made with a tape measure and pen, with the participant sitting on a chair without backrest, so that two points are marked bilaterally [38]: the first mark will be 5 cm lateral to the spinous process of L3 [39] and the second will be 5 cm lateral to the spinous process of L5 [40]. A third mark will be made on the anterior tibial muscle of the right lower limb in order to have a control [41, 42]. To measure pressure pain threshold, the circular algometer probe, which is 1 cm^2^ in area, will be positioned at a 90-degree angle on the skin and will be pressed with approximately 50 kPa/s of speed. The instruction given to the participants will be to push the button when the feeling of pressure or discomfort becomes painful. The measurements in kPa will be repeated three times at each point with a 30-s interval between measurements [43]. The average of the three measurements will be used for data analysis. If the participant does not report pain at a pressure of 1000 kPa, the test will be interrupted, and this value will be adopted as the pressure pain threshold. The intrarater reliability of the pressure pain threshold was tested prior to data collection and was adequate (ICC = 0.92).

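### The only stated adverse-event window is the intervention period, which leaves 16 to 18 of 26 follow-up weeks and two of the three test visits without stated collection of discrete harms

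*Protocol article*

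**What the plan says.** The protocol article, under Randomization and interventions, states: "Adverse events will be collected during the intervention period". No other sentence deals with adverse events. The same section defines the period as "16 individual, twice-weekly exercise sessions lasting 60 min each over a period of 8 weeks". It allows missed sessions to be made up, provided that "the intervention period and the make-up sessions do not exceed 10 weeks, when the treatment will end".

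Follow-up runs well beyond that. Under Assessment, "The assessment of the outcomes will be repeated eight weeks and six months after randomization in the same place", and for baseline, "The initial assessment will be conducted prior to the random distribution of the patients into the treatment groups".

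The visits include demanding physical tests: five chair stands at speed, walking at maximal pace, and strength testing of three hip muscle groups on both sides, where practice efforts are "followed by two repetitions with maximum isometric contraction for each muscle group". Table 2 schedules dynamic balance and muscle strength before randomization, at 8 weeks and at 6 months. These columns are separate from the intervention-period column, and there is no adverse-event row.

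Under Statistical analysis, the article adds that no further outcome is collected once a patient drops out of treatment.

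**The concern.** Benefit is followed to 6 months, but the stated harm window closes at week 8 to 10. The patients are 65 to 85 years old, and the Background itself links ageing to postural instability and disability. Two kinds of event have no stated place to be recorded:

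- falls, injuries, transient flares and care sought between the end of treatment and the 6-month visit;
- injuries or flares caused by the trial's own tests at baseline and at 6 months.

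The request to avoid other treatment also covers only the intervention period, so care sought later is neither discouraged nor recorded. If the report lists no late events, that will reflect the window and will not be evidence that none occurred. Patients who stop treatment because of harm are the most exposed, because the dropout rule can be read as ending all data collection for them.

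**Working it through.** The article gives no figure for adverse events, so there is none to reproduce. The check is calendar arithmetic and a comparison of the sections.

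**Inputs**
- Planned treatment: 8 weeks (Randomization and interventions).
- Longest treatment with make-up sessions: 10 weeks (same section).
- Last visit: 6 months after randomization (Assessment; Table 2), taken as 26 weeks.
- Assumption: treatment starts at randomization. A delayed start would shift the window and shorten the later gap by the same delay.

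**Time without stated collection** = length of follow-up − length of treatment
- Planned course: 26 − 8 = 18 weeks; 18/26 = 69%.
- Longest course: 26 − 10 = 16 weeks; 16/26 = 62%.
- With calendar months (26.1 weeks) the gaps are 18.1 and 16.1 weeks, so the rounding does not matter.

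**Test visits against the window**

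| Visit | Position relative to the window |
|---|---|
| Baseline | Outside: before randomization |
| 8 weeks | Inside for patients still in make-up sessions; outside for those who have finished |
| 6 months | Outside: at least 16 weeks after treatment ends |

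Two of the three test visits are therefore outside for every patient, and the third is outside for some. If the two maximal repetitions apply to each side, one visit involves 3 muscle groups × 2 sides × 2 repetitions = 12 maximal contractions, besides the chair stands and the fast walk.

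**What the other measures still capture.** Pain intensity, disability and global perceived effect are assessed at 6 months, the last on a scale from −5 to 5. A patient who is lastingly worse would be visible there. A fall, an injury that has healed, a flare that has settled or a course of care would not be.

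**After the change.** If collection runs to the 6-month visit, the uncovered time after randomization is 0 weeks.

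**The case against.** The best defence is that the window matches exposure. Supervised exercise ends by week 10, no harm outcome is listed, and the article nowhere claims safety to 6 months. Recording events while patients are being treated is a defensible choice and contradicts nothing in the text. The tests are the same in both arms, and the baseline ones precede randomization, so events during them say little about Pilates against aerobic exercise. In algometry the participant signals when pressure becomes painful, and 1000 kPa is only the point where the test stops; this point does not rest on that test.

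Much of this stands, and it keeps the point modest. It does not remove it: harm from research procedures deserves a record whichever arm the patient is in, and the article fixes a window where it could have left the detail to a fuller document.

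A reader might go further in two ways that the article does not support:

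- **That there would be no harm data at all at 6 months.** This is too strong, because sustained worsening is measured then by the blinded assessor.
- **That the comparison of harms is biased because each arm has its own unblinded therapist.** The article says, for example, "The Pilates Group will be supervised by a physical therapist certified in Pilates with four years of experience with the method", and names a different therapist for the aerobic arm. It does not say who records adverse events or how. Unequal recording between arms is conjecture, and no size can be put on it from this document.

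**Conclusion.** The point holds as a limited gap in the safety data. Discrete harms have no stated collection for 16 to 18 of 26 weeks (62% to 69%), nor at the baseline and 6-month test visits. The size assumes 26 weeks for 6 months and treatment starting at randomization. The article does not say that collection happens only in the intervention period; that follows from its being the one window given. The missing row in Table 2 adds little by itself, since the table also omits pressure pain threshold, which is a listed outcome.

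The primary efficacy estimate is unaffected. With 74 patients planned, and 15% loss to follow-up allowed for, harm data will be descriptive whatever the window. This is a worthwhile, inexpensive improvement and does not put the trial's main conclusion at risk.

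**What to change.** 1. Under Randomization and interventions, change the sentence so that collection runs from the baseline assessment to the 6-month visit.
2. At the 8-week and 6-month visits, give the same short written form to both arms. It asks about falls, injuries, new or worse pain and care sought, with dates. The patient completes it after all outcomes are measured, and it goes unread to a researcher other than the blinded assessor. An interview by the assessor would risk revealing the arm at 8 weeks, before the 6-month outcomes are measured.
3. Record events that occur during the tests at all three visits.
4. Under Statistical analysis, state that the rule on treatment dropouts does not stop adverse-event collection. Otherwise the patients most likely to have been harmed may never be asked.
5. Report the number of patients with at least one event by arm, descriptively, separately for the treatment period, the post-treatment period and test-related events.
6. Add an adverse-event row to Table 2.

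The cost is two amended sentences, one form, a table row and a few minutes at visits already planned. The main weakness is recall over 16 to 18 weeks at the 6-month visit, so minor events will be under-reported.

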### Sample size

The study was designed to detect a clinically significant 2-point difference in pain intensity assessed by the Pain Numerical Rating Scale (estimate for standard deviation = 2.5) and a 5-point difference in disability assessed by the Roland Morris Disability Questionnaire (estimate for standard deviation = 6.5) [49, 50] eight weeks after randomization, using a two-tailed t-test of difference between means and assuming α = 0.05, statistical power of 80% [51], and loss to follow-up of 15%. Estimations indicated that 34 patients per group will be required using pain intensity to calculate sample size, and 37 patients per group using disability. Therefore, the biggest number resulting from sample size calculation will be considered, which corresponds to 74 patients. To reach this number, the study will be promoted in community newspapers and on the internet.

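### The stated 34 and 37 patients per group do not follow from 80% power with 15% loss, so either the stated power or the stated loss allowance is wrong; the error is conservative

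*Protocol article*

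**What the plan says.** The Sample size section of the protocol article gives every input to its calculation.

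- Pain: a "clinically significant 2-point difference in pain intensity assessed by the Pain Numerical Rating Scale", with "estimate for standard deviation = 2.5".
- Disability: "a 5-point difference in disability assessed by the Roland Morris Disability Questionnaire", with "estimate for standard deviation = 6.5".
- Test and error rate: "using a two-tailed t-test of difference between means", "assuming α = 0.05".
- Power and attrition: "statistical power of 80% [51], and loss to follow-up of 15" per cent.

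The result is given as "Estimations indicated that 34 patients per group will be required using pain intensity to calculate sample size, and 37 patients per group using disability". The larger figure is taken, for a total of 74. The Abstract randomises 37 to each group, so 37 is the number enrolled and nothing is added for loss at a later step.

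**The concern.** A sample-size statement should be reproducible from the inputs printed beside it, and this one is not. The gap of 3 and 4 patients per group is too large for a rounding convention. Both figures miss in the same direction, so a slip in one of them is an unlikely cause.

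What is at stake is what the trial was designed to do. A reader cannot tell whether 74 was meant to give 80% power after losses, some higher power after losses, or 90% power with no room for losses. The allowance for loss matters here because the Statistical analysis section says that outcomes stop being collected once a patient drops out of treatment, so each drop-out lowers the evaluable number. The Discussion also cites the sample calculation in support of the trial's quality.

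**Working it through.** **Inputs**, all from the Sample size section: differences of 2 (SD 2.5) and 5 (SD 6.5), two-tailed two-sample t-test, α = 0.05, power 80%, loss 15%. Allocation is 1:1 (Abstract, 37 and 37).

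**Standardised differences.** Pain: d = 2/2.5 = 0.800. Disability: d = 5/6.5 = 0.769.

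**Method.** As a first step, the normal approximation per group is n = 2(z₀.₉₇₅ + z_power)²/d². The t-test figure solves the noncentral t power equation with 2n − 2 degrees of freedom and noncentrality d√(n/2). Loss L is applied as n/(1 − L); the cruder n × (1 + L) is shown as a check.

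**Attempt to reproduce the plan's figures at 80% power and 15% loss**

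| Step | Pain | Disability |
|---|---|---|
| Normal approximation, evaluable | 24.5 → 25 | 26.5 → 27 |
| after loss, n/0.85 | 30 | 32 |
| after loss, n × 1.15 | 29 | 32 |
| t-test, evaluable | 25.5 → 26 | 27.5 → 28 |
| after loss, n/0.85 | 26/0.85 = 30.6 → **31** | 28/0.85 = 32.9 → **33** |
| after loss, n × 1.15 | 26 × 1.15 = 29.9 → 30 | 28 × 1.15 = 32.2 → 33 |
| Stated in the plan | **34** | **37** |

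The closest variant is 31 and 33. It misses by 3 and 4 per group, or 2 × 33 = 66 in total against 74. A one-sided test would need fewer still.

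**Which inputs do give 34 and 37?** All three routes below use the t-test at two-sided α = 0.05.

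- 90% power, no loss allowance: 33.8 → 34 and 36.5 → 37. Power is 90.2% for pain at 34 (89.3% at 33) and 90.4% for disability at 37 (89.6% at 36).
- 85% power, 15% add-on: 29.05 × 1.15 = 33.4 → 34 and 31.34 × 1.15 = 36.0 (36.04 before rounding) → 37.
- 80% power, 30% add-on: 26 × 1.3 = 33.8 → 34 and 28 × 1.3 = 36.4 → 37.

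The first contradicts both the stated power and the stated loss, the second only the power, the third only the loss.

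**What 37 per group delivers.** With 15% loss, 37 × 0.85 = 31.45, so about 31 are evaluable.

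| Evaluable per group | Pain | Disability |
|---|---|---|
| 37 (no loss) | 92% | 90% |
| 31 (15% loss) | 87% | 85% |

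Eighty per cent power for disability needs 28 evaluable, so it holds up to a loss of 1 − 28/37 = 24%.

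**If 90% had been the target with 15% loss:** 34/0.85 = 40 and 37/0.85 = 43.5 → 44 per group, or 88 in total.

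**The case against.** The strongest reply is that nothing is lost. The discrepancy is 4 per group in the safe direction, the randomised numbers are consistent throughout the article, and the analysis is unaffected. That stands as a limit on the consequence: this is a reporting error about the design, with no shortage of patients. It does not remove the point, because the article states the inputs and the output together and they disagree.

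A second reply concerns the cause. A reader might infer from the exact match that the calculation was run at 90% power and the loss allowance forgotten. The article does not support that as a conclusion. 85% power with a 15% add-on gives the same pair, and on that reading the allowance was applied and only the power is misreported. This objection stands in full: the 90% route is one candidate among several.

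The article is a condensed document, but that does not explain the gap. It prints all the inputs, and the contradiction lies within them.

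**Conclusion.** The point holds as a failure to reproduce. On the stated inputs the requirement is 31 (pain) and 33 (disability) randomised per group, 66 in total, against the stated 34, 37 and 74. Either the 80% or the 15% is not what was used, and the article cannot show which.

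A reader might go on to infer that the trial lacks the 80% power it claims after losses. The figures say the opposite: with about 31 evaluable per group it has about 87% for pain and 85% for disability. A shortfall arises only against a 90% target, which the article does not state.

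Nor should a reader take the margin as enough to split α between the two primary outcomes. At α = 0.025 with 31 evaluable per group, power is 80.0% for pain but only 76.5% for disability.

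These results rest on the article's own differences and SDs, equal allocation, an unadjusted t-test and equal loss in both groups.

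**What to change.** Keep 74 and correct the Sample size paragraph.

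1. State which power, loss allowance and rounding rule produced 34 and 37.
2. Make inputs and outputs agree. If 80% power and 15% loss remain the requirement, the sizes are 31 and 33 per group, with 37 given as the number chosen.
3. Report what 37 per group delivers with 15% loss: about 87% power for pain and 85% for disability.
4. If 90% power was intended, say that 37 per group reaches it for disability only without losses.

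The cost is one reworded paragraph. Enrolment, randomisation and analysis do not change.
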